## Abstract

**Introduction:**

Shoulder pain is common and the prognosis is often unfavourable. Dutch guidelines on the treatment of shoulder pain in primary care recommend a corticosteroid injection or a referral to exercise therapy, if initial pain management fails and pain persists. However, evidence of the effectiveness of a corticosteroid injection compared with exercise therapy, especially in the long term, is limited. This trial will assess the clinical effectiveness and cost effectiveness of a corticosteroid injection compared with physiotherapist-led exercise therapy over 12 months follow-up in patients with shoulder pain in primary care.

**Methods and analysis:**

The SIX Study is a multicentre, pragmatic randomised clinical trial in primary care. A total of 213 patients with shoulder pain, aged ≥18 years presenting in general practice will be included. Patients will be randomised (1:1) into two groups: a corticosteroid injection or 12 sessions of physiotherapist-led exercise therapy. The effect of the allocated treatment will be assessed through questionnaires at 6 weeks and after 3, 6, 9 and 12 months. The primary outcome is patient’s reported shoulder pain-intensity and function, measured with the Shoulder Pain and Disability Index, over 12 months follow-up. Secondary outcomes include cost effectiveness, pain-intensity, function, health-related quality of life, sleep quality, patient’s global perceived effect, work absence, healthcare utilisation and adverse events. Between group differences will be evaluated using a repeated measurements analysis with linear effects models. A cost-utility analysis will be performed to assess the cost effectiveness using quality-adjusted life years from a medical and societal perspective.

**Ethics and dissemination:**

This study was approved by the Medical Ethics Committee of Erasmus MC University Medical Center Rotterdam (MEC 2020-0300). All participants will give written informed consent prior to data collection. The results from this study will be disseminated in international journals and implemented in the primary care guidelines on shoulder pain.

**Trial registration number:**

Dutch Trial Registry (NL8854).

Strengths and limitations of this studyThis is a large pragmatic randomised controlled trial that aims to evaluate two treatment options recommended by the guidelines in the management of persistent shoulder pain in general practice, a corticosteroid injection compared with exercise therapy.In addition to the clinical effectiveness, a cost-effectiveness analysis will be performed for both treatments.This study has a long follow-up period of 12 months, allowing for the analysis of the long-term (cost-)effectiveness of both treatments.The pragmatic nature of this trial has its drawbacks, however, it will provide a true reflection of both treatments applied in current practice.

## Introduction

### Background and rationale

Shoulder pain is the third most common musculoskeletal complaint in primary healthcare.^1–3^ The estimated incidence is reported at 30.3 per 1000 person-years.^3^ The prognosis for shoulder pain is often unfavourable. Only 50% of people presenting with a new episode of shoulder pain in primary care show complete recovery within 6 months.^4^ In general, apart from pain, patients with shoulder pain report having functional limitations which can reach a level of severity whereby they preclude work-related tasks.^5^ Work absence and treatment of shoulder pain generate high costs to society and healthcare.^6 7^ A recent cost-estimation study for patients with shoulder pain consulting in primary care in Sweden estimated the mean annual costs at €4139 per patient, with sick leave accounting for more than 80% of the total costs.^7^

Guidelines for the management of shoulder pain provide treatment options based on the initial diagnosis of the general practitioner (GP) and the severity of the pain.^8 9^ The recommended management options in the guidelines are focused on controlling pain and restoring or maintaining shoulder function. The recently updated primary care guideline for shoulder pain, issued by the Dutch College of General Practitioners (NHG) in 2019, recommends a stepped-care approach. In the first step, GPs are advised to start the treatment with advice and, if necessary, prescribe analgesics. If pain persists, the GP is recommended to either prolong or adjust analgesics, administer a local corticosteroid injection in case of severe pain or refer the patient to a physiotherapist for exercise therapy in case of (impending) dysfunction.^8^ Although the guideline recommends exercise therapy or corticosteroid injection when shoulder pain persists, the guideline acknowledges the lack of evidence to favour one option over the other.

A systematic review by Steuri *et al* on randomised controlled trials (RCTs) comparing corticosteroid injection(s) to exercise therapy showed that injections have statistically significant, but small effect on pain in the short term, generally within 6 weeks after the intervention, but not at longer follow-up time intervals (3–6 months).^10^ Given the low quality of most of the included studies and high level of heterogeneity, the authors concluded that larger, high quality trials are required. Moreover, the authors call for health economic evaluations alongside such trials to assess comparative cost effectiveness and cost utility. A similar call came from the Cochrane review by Page *et al* on manual therapy and exercise for rotator cuff disease; ‘high quality RCTs are needed to establish the benefits and harms of exercise interventions that reflect actual practice, compared with placebo, no intervention or active interventions with evidence of benefit (eg, glucocorticoid injection)’.^11^

Given the high incidence and costs associated with shoulder pain and the lack of high quality evidence to underpin current clinical practice and guideline recommendations, the recently published National Research Agenda by the NHG listed research on the effectiveness of corticosteroid injections for shoulder pain in general practice as a top priority.^12^ We have therefore designed an RCT to compare the clinical and cost effectiveness of corticosteroid injections and physiotherapist-led exercise therapy as primary care management interventions for patients with shoulder pain.

### Objectives

The primary objective of the Shoulder Injection and eXercise (SIX) trial is to compare the clinical effectiveness of a local corticosteroid injection to physiotherapist-led exercise therapy for shoulder pain in primary care over 12 months of follow-up. The main secondary objective is to compare the cost effectiveness of both treatments over a 12-month follow-up period.

## Methods and analysis

### Trial design/study setting

The study is a randomised, multicentre, open label, parallel group, pragmatic clinical trial. Patients will be recruited in Dutch general practices. GPs will select patients presented with shoulder pain who are suitable for both a local corticosteroid injection and physiotherapist-led exercise therapy. GPs will refer these patients to the SIX research team, who will further assess all potential patients for eligibility and will undertake informed consent procedures.

### Eligibility criteria

#### Inclusion criteria

Patient has contacted their GP with shoulder pain due to subacromial pain syndrome or glenohumeral disorders.Aged 18 years or older.Qualified for both a local corticosteroid injection and physiotherapist-led exercise therapy, as indicated by the GP.Able to understand spoken and written Dutch language.

#### Exclusion criteria

Shoulder pain due to recent serious trauma, malignancy, systemic rheumatologically disease, neurological or cardiac disease.^8^Shoulder pain due to instability of the glenohumeral joint, disorders of the acromioclavicular or sternoclavicular joint, or neck pain with additional shoulder pain.Treatment of the affected shoulder with corticosteroid injection or physiotherapy in the last 6 months.A history of serious shoulder trauma, such as fractures, ruptures, luxation or surgery.Contraindications for corticosteroid injection.Current use of oral corticosteroids.

For participants with bilateral shoulder pain, the most painful shoulder will be taken as the study shoulder.

### Parallel cohort study

Patients with shoulder pain who are not eligible for trial participation or patients who are eligible but do not want to be randomised, for example, due to strong treatment preferences, will be invited to participate in a parallel cohort study. With their consent, these patients will be assessed using the same outcome measures at similar time points. In addition, these patients will complete a questionnaire regarding their treatment preferences and reasons for not wanting to participate in the trial (if applicable) at baseline. This information will provide important information regarding the recruitment process by indicating if and why recruitment may be suboptimal or failing. Furthermore, the parallel cohort study will provide the unique possibility to compare baseline characteristics of randomised participants to those who were not eligible or not willing to be randomised and outcomes following their (preferred) treatment.

We anticipate recruiting around 600 patients to this parallel cohort study. All cohort participants who are not eligible for the RCT will be informed that if the initial GP treatment fails and they consider re-consultation, they are potentially eligible for the RCT. They can contact the SIX research team for receiving additional information regarding the trial and to initiate the consent procedure for the trial.

### Interventions

#### Corticosteroid injection

The corticosteroid injection will be delivered by the GP. The corticosteroid injection will consist of 40 mg triamcinolone acetonide (Kenacort-A 40), possibly in combination with a local anaesthetic agent, lidocaine 10 mg, at the discretion of the GP in accordance with the NHG guideline for shoulder pain.^8^

The site of the injection, subacromial or intra-articular, will depend on the initial diagnosis of the GP. Subacromial injections will be administered to participants diagnosed with subacromial pain syndrome and intra-articular injections on participants with glenohumeral joint pain. GPs are advised to follow the instructional videos on subacromial and intra-articular injection published by the NHG.^13^ All participating GPs will be invited for an optional shoulder injection training by an experienced doctor of orthopaedic medicine at the Erasmus MC.

Consultations with the GP will be coordinated so that participants typically receive their injection within 1 week of randomisation. In line with the guideline, a maximum of two injections will be permitted per patient, with the second injection, when considered necessary, offered 2–4 weeks after the first injection. Any participant receiving a second injection will have the date of administration recorded in their case report form.

#### Physiotherapist-led exercise therapy

Participants randomised to physiotherapist-led exercise therapy will be referred to one of the local physiotherapists. Preferably the physiotherapist is affiliated with the Dutch Shoulder Network (SNN). The SNN is an umbrella organisation for regional shoulder networks of physiotherapist practices. All affiliated physiotherapists have to complete a 2-day entry course on shoulder pain, accredited by the Royal Dutch Society for Physiotherapy (KNGF).

The exercise therapy will consist of a maximum of 12 treatments of around 30 min under the supervision of the physiotherapist over a course of 12–14 weeks. In addition, all participants will receive home-based exercise at the discretion of the physiotherapist. The intensity of the exercise is based on tissue irritability and the capacity of the patient. Pain during or after exercise is allowed, as long as there is no night-time pain and the pain returns to pre-training levels within 24 hours. Physiotherapist will be requested not to use massage, laser therapy, ultrasound therapy, transcutaneous electrical nerve stimulation, dry needling or acupuncture, given lack of evidence for effectiveness.^14^ All participating physiotherapists will receive a brief guideline developed in cooperation with the SNN describing the criteria for exercise therapy.

#### Co-interventions

This is a pragmatic clinical trial designed to evaluate the effectiveness of corticosteroid injections compared with physiotherapist-led exercise therapy for shoulder pain in real-life routine practice conditions. Therefore, participants will be instructed to continue their usual medication as discussed with their GP. Co-interventions after randomisation will be allowed and will be monitored through medical record review and questionnaires. This includes cross-over between interventions, which is estimated to occur in 20% of participants based on the number of patients receiving an injection and referral for exercise therapy in the ‘usual care’ treatment arm of a recent RCT.^15^

### Outcomes

Table 1 shows an overview of the time schedule of enrolment, interventions and all assessments for participants. The selection of outcome measures has been based on the core outcome set published by The Outcome Measures in Rheumatology (OMERACT) Shoulder Working Group.^16^ The primary outcome is shoulder pain-intensity and function measured using the Shoulder Pain and Disability Index (SPADI) total score over 12 months post randomisation.^17^ The SPADI is the most commonly used measure to assess pain-intensity and disability.^18^ The Dutch version of the SPADI has good psychometric properties.^19 20^

**Table 1 T1:** Time schedule for enrolment, interventions and assessments for participants

Time point	Pre- randomisation	Baseline (T0)	6 weeks (T1)	3 months (T2)	6–9–12 months (T3–T4–T5)*
Enrolment					
Diagnosis	X				
Eligibility screening	X				
Informed consent	X				
Randomisation†		X			
Interventions					
Corticosteroid injection†		X			
Physiotherapist-led exercise therapy†					
Assessments					
Sociodemographics		X			
Current shoulder episode (location, duration, cause, course, stiffness)		X			
Previous shoulder episodes (history, treatments)		X			
Other current pain locations (pain manikin)		X			
Other relevant medical issues		X			
Psychological prognostic factors (HADS, FABQ)		X			
Current medical use for the shoulder pain		X			
Treatment preferences		X			
Treatment expectations		X			
Outcomes					
Pain and function (SPADI)		X	X	X	X
Medical costs (MCQ)			X	X	X
Global perceived effect (GPE)			X	X	X
Productivity costs (PCQ)			X	X	X
Health-related quality of life (EQ-5D-5L)		X	X	X	X
Sleep quality (SQS)		X	X	X	X
Side effects			X	X	
Serious adverse events (SAEs)			X	X	X

*At these time points the indicated outcome measures will be repeated.

†Randomisation occurs after baseline measurements are taken.

EQ-5D-5L, five-level version of the well-validated EuroQol Five-Dimensional Questionnaire; FABQ, Fear-avoidance Beliefs Questionnaire; HADS, Hospital Anxiety and Depression Scale; MCQ, Medical Cost Questionnaire; PCQ, Productivity Cost Questionnaire; SPADI, Shoulder Pain and Disability Index; SQS, Sleep Quality Scale.

Secondary outcomes include incremental costs per quality-adjusted life year (QALY) gained, using both the medical as well as the societal perspective, over 12 months post randomisation. Medical costs will be measured using the Medical Cost Questionnaire (MCQ) and societal costs will be measured using the Productivity Cost Questionnaire (PCQ).^21^ QALY will be measured using the five-level version of the well-validated EuroQol Five-Dimensional Questionnaire (EQ-5D-5L) score.^22^

Other secondary outcomes will be clinical effectiveness and cost effectiveness of the randomised treatments in the short term (6 weeks, 3 months) and medium term (6 months, 9 months). In addition, secondary outcomes will include subdomains (pain and function) of the SPADI, health-related quality of life (EQ-5D-5L), sleep quality measured with the Sleep Quality Scale,^23^ participant’s perceived recovery using the global perceived effect questionnaire,^16^ work absence as measured by the PCQ, healthcare utilisation as measured by the MCQ, side effects assessed at short term post randomisation and serious adverse events (SAEs) occurring post randomisation.

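### No baseline measure of work absence is scheduled, so a chance imbalance in sick leave at entry can be neither shown nor directly adjusted for, and the societal-cost and work-absence comparisons lose precision

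*Protocol article*

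**What the plan says.** Table 1 (Outcomes) is presented as the overview of enrolment, interventions and all assessments. Its rows for the two cost instruments are "Productivity costs (PCQ) X X X" and "Medical costs (MCQ) X X X". Both start at 6 weeks and leave the baseline cell empty. The quality-of-life row, "Health-related quality of life (EQ-5D-5L) X X X X", has one mark more, at baseline, as do SPADI and sleep quality.

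These instruments carry important outcomes:

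- Objectives: "The main secondary objective is to compare the cost effectiveness of both treatments over a 12-month follow-up period".
- Outcomes: the secondary outcomes include "work absence as measured by the PCQ, healthcare utilisation as measured by the MCQ". The PCQ is also the source of societal costs. Cost effectiveness is to be reported at 6 weeks and 3, 6 and 9 months as well as over 12 months.
- Background and rationale: a Swedish primary care study put the mean annual cost at €4139 per patient, "with sick leave accounting for more than 80% of the total costs".

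The baseline column does hold related items: sociodemographics (contents not listed), current episode including its duration, HADS, FABQ, "Current medical use for the shoulder pain X" and "Previous shoulder episodes (history, treatments) X". Allocation describes concealed web-based randomisation in random blocks and states no stratification. The covariates named under Primary analyses are age, gender, duration of pain, neck pain and history of shoulder pain. Secondary analyses names no covariate for costs or work absence.

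**The concern.** Unlike perceived recovery, which needs no baseline because it measures change, work absence can exist before randomisation. A participant who is off work at entry brings that absence into the first follow-up periods whatever the allocation. It weighs most in the 6-week and 3-month cost analyses that the article also plans.

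If the arms happen to differ in the number already on leave, the difference passes into the societal incremental cost and the work-absence regressions. With no baseline PCQ, the baseline table cannot show it and the models cannot adjust for it directly. The two sides of the cost-utility ratio are also treated unequally: QALYs can be adjusted for baseline EQ-5D-5L, while productivity costs have no counterpart.

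A later analysis plan can choose covariates, but it cannot supply a value that was never collected.

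**Working it through.** **Figures in the article.** The schedule itself has no figure to reproduce. The sample size, used below as n, does reproduce: 2 × (1.960 + 1.282)² × 20² / 10² = 84.1, so 85 per arm, and 170 / 0.8 = 212.5, so 213 randomised, about 106 per arm. The cited sick-leave cost is more than 0.8 × €4139 = €3311 per patient per year.

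**1. Does the missing baseline bias the comparison?** Simulation of 10,000 trials for each correlation, 85 per arm, no treatment effect, normal outcome, no baseline adjustment, correlation ρ between baseline and follow-up of 0.3, 0.5 and 0.7. The mean error was at most about 0.003 SD, and the type I error was 4.8% to 5.2%. There is no bias and no inflation of error.

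**2. How large can a chance imbalance be?** The SE of the between-arm difference in the proportion on leave at entry is √(2p(1−p)/n). The article does not give the prevalence p, so 10%, 20% and 30% are assumed.

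| p (assumed) | SE, n = 85 | 95% range, n = 85 | Chance of a gap ≥ 10 points, n = 85 | Same, n = 106 |
|---|---|---|---|---|
| 10% | 4.6 points | ±9 points | 3% | 1.5% |
| 20% | 6.1 points | ±12 points | 10% | 7% |
| 30% | 7.0 points | ±14 points | 16% | 11% |

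For scale in euros, assume p = 10% and €10,000 to €20,000 for each person on leave at entry. The SD of the difference in numbers is √(2 × 106 × 0.1 × 0.9) = 4.37 participants. A one-SD imbalance then shifts the mean cost difference by 4.37 × 10,000 / 106 = €412 to 4.37 × 20,000 / 106 = €824 per patient. Every input except the arm size is assumed.

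**3. What would baseline adjustment gain?** Linear adjustment multiplies the variance of the difference by 1 − ρ². The article gives no ρ.

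| ρ (assumed) | Variance cut | SE cut | 170 analysed act like | Simulated SE, unadjusted v adjusted (SD units) |
|---|---|---|---|---|
| 0.3 | 9% | 5% | 170 / 0.91 = 187 | 0.153 v 0.146 |
| 0.5 | 25% | 13% | 170 / 0.75 = 227 | 0.154 v 0.134 |
| 0.7 | 49% | 29% | 170 / 0.51 = 333 | 0.153 v 0.110 |

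**4. What do the existing baseline items offer?** SPADI, EQ-5D-5L, FABQ and episode duration may be related to absence but do not measure it. Sociodemographics may include work status; even so, being employed is not the same as being on leave. For medical costs the position is better: previous treatments and current medical use are asked, and the exclusion criteria remove anyone whose affected shoulder had an injection or physiotherapy in the last 6 months.

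**The case against.** The strongest reply is that this is ordinary sampling variation. Allocation is concealed and 1:1, and follows the baseline questionnaire, so prior leave is balanced in expectation. The planned bootstrap and regression intervals already contain the variation. That stands. A reader might infer that carried-over sick leave biases the cost comparison; the randomised design does not support this, and step 1 confirms it.

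A reader might also infer that a few participants on long-term leave would dominate the societal result. The documents do not support that either. The €412 to €824 shift is about 10% to 20% of €4139, assumes that everyone on leave at entry incurs the full cost, and is not set against the SE of the incremental cost, which cannot be derived from the article. The 80% share comes from one Swedish study and does not say how much of the leave was already running at consultation.

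Nor is the gap beyond all repair. The baseline proxies allow partial adjustment. The article plans medical record review for co-interventions, and such records might also yield earlier healthcare contacts. The medical-cost half is therefore weak.

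Finally, an article need not list the contents of its sociodemographic items or the covariates of its cost model. This is fair, and neither is criticised here. The schedule of the PCQ, however, is stated outright in Table 1, and that is what the point rests on.

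**Conclusion.** The point holds as a loss of precision and of control over chance imbalance in the main secondary objective and the work-absence outcome. It does not touch the primary outcome, the sample size or the validity of inference.

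Its size depends on assumptions. The variance forgone is 9% to 49% for ρ from 0.3 to 0.7, and the 95% range of chance imbalance is ±9 to ±14 percentage points for 10% to 30% on leave at entry with 85 per arm. At the low end the gain is modest (5% of the SE). At the high end it is worth about as much as doubling the analysed sample for these outcomes. The case is mainly about the PCQ; for the MCQ it is much weaker. The change is worth making because it is cheap and because the value is best collected before randomisation.

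**What to change.** Add the PCQ work-status and recent-absence items to the baseline questionnaire in Table 1, completed before randomisation and with the same recall period as the follow-up forms. Report them in the baseline table, and name the baseline value as a covariate for societal costs and work absence. Baseline MCQ contact items are optional.

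The cost is a few extra minutes on a questionnaire that participants already complete, and a small amendment; no added visit or staff. The article reports recruitment as ongoing in November 2020, so those already randomised would lack the value. For them, use the available baseline proxies or imputation. Whether the value is missing would depend on the date of enrolment rather than on the arm, so this need not bias the comparison, but the gain in precision shrinks with each participant enrolled before the change.
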